### **fMRI**

24 participants in Edinburgh will be allocated to undergo functional magnetic resonance imaging (fMRI) of the brain at 3 months (as long as they satisfy safety issues related to the procedure). The study of fMRI requires the need to contrast periods of brain activation (induced by pain) with periods of rest. Therefore, subjects will be asked to lie still and a weighted ball will be applied to the abdomen at regular intervals during the procedure (block design with alternating periods of 16 seconds of 'pain' and 16 seconds of 'rest') (Liu et al, 2001). Pain levels will vary per subjects so we will include a 'rating scale' to allow us to do a regression analysis of fMRI level of activation as a function of the level of pain. Pain levels also vary according to the woman's menstrual cycle (reference). We will carry out the fMRI at the same stage of each participant's cycle. We will take a blood sample to measure hormone levels. Each fMRI will last ~30 mins: structural scans T1 and T2 (~10 mins), fMRI scan 16 seconds on/off repeated 20 times (~10 mins) and time for subject to get into and out of scanner and apply weighted ball in position (~10 mins). Discontinuation rules in case of patient distress will be as follows. Before the fMRI, we will assess the level of discomfort associated with the 'ball test' (plus obtain the 'rating'). We will also use a thermal resistor to deliver noxious thermal stimulation of a pre-determined intensity (the temperature adjusted for each subject to produce a rating of this intensity) as has been successfully used previously (VINCENT K, et al. Pain 2011 152(9):1966-75). Participants will also be given the opportunity to withdraw from this component of the study pre-fMRI. In addition, in the scanners, there is a button that participant can press to stop the scan. This will allow participants to withdraw from this component of the study during the fMRI. The fMRI studies will be performed in Edinburgh (3T Siemens MRI), supported by the Scottish Imaging Network, SINAPSE. We will calibrate the fMRI protocols by asking up to 4 healthy volunteers to undergo this procedure. They will complete a CRIC consent and safety form before taking part.

## **8 DATA COLLECTION**

**Screening:** A member of the research team will carry out a screening visit to assess eligibility. All data will be recorded on a CRF and transferred to a secure database. Participants will be reminded to use effective contraception for the duration of the study and for one week after their last dose of gabapentin.

**Participant Log:** The clinical research team will keep an electronic log of women who fulfil the eligibility criteria, women who are invited to participate in the study, women recruited and women who leave the trial early. Reasons for non-recruitment (eg non-eligibility, refusal to participate, administrative error) will also be recorded. We will attempt to collect reasons for non-participation from women who decline to take part after previously providing contact details. During the course of the study, we will document reasons for withdrawal from the study and loss to follow-up.

**Treatment diaries:** details are documented in Section 6.5. All medications taken after screening and any medication other than the trial treatment taken during the study will be recorded in the treatment diary. This includes prescription and non-prescription treatment such as contraceptives, vitamins, topical preparations, herbal preparations and non-pharmacological therapies. Permissible and excluded concomitant medications are itemised. These restrictions apply during the period from screening to end of treatment. The permissible supplemental pain medications may be initiated at any time during the study (unless specified otherwise).

Questionnaires: A questionnaire will be given to all participants at randomisation (0 months) and at 3 months. This will include questions to capture the baseline demographic and clinical characteristics of the participants and include the following validated tools:

1. Neuropathic Pain Questionnaire (NPQ) (including Lickert pain score)
2. Brief Pain Inventory (BPI)
3. Pain Disability Questionnaire (PDQ)
4. Hospital Anxiety and Depression Score (HADS)
5. EQ5D QoL
6. WHO QoL
7. MYMOP patient-generated outcome questionnaire

A further questionnaire will also be given to all participants at 6 months which will include the above and additional questions on whether they believed they were receiving Gabapentin or placebo, and also questions on acceptability of the allocation medication (and compliance) and on the acceptability of the above data collection methods. Lastly, we will ask the participants to complete a brief anonymous questionnaire once they have submitted their treatment diaries to assess level of adherence to diary keeping.

Focus groups: A purposive sample (based on age, social class and severity of symptoms) of 10 Edinburgh women (including some undergoing fMRI) and 10 Aberdeen women will be invited to participate in focus group discussions of the trial experience. Women who do not wish to participate in a focus group will be offered individual interviews using the same interview schedule. This will enable important issues arising in the focus groups to be explored in greater depth. Up to 20 interviews will be performed. Group/individual interviews will be audio-recorded, transcribed verbatim and analysed thematically to identify the issues of importance to participants.

## 9 STATISTICS AND DATA ANALYSIS

### 9.1 SAMPLE SIZE CALCULATION

We have used a confidence interval (CI) approach (Thabane 2010) to estimate the sample size to establish feasibility based on a loss to follow-up of <20%. A 95% CI for 20% of 60 patients (12/60) is 11% to 32%. We estimate that we will recruit ~3-4 patients per month from each centre and aim to recruit 60 patients over a nine-month recruitment period. Each centre performs 6-7 laparoscopies per month that fit the inclusion criteria. A power calculation for the fMRI sub-studies is more difficult due to the complexity of the model (Mumford and Nichols 2008). The signal noise ratio changes in space and therefore power depends on the effect size that differs from region to region. We have estimated that we will need to recruit 24 women to determine where there are differences using fixed effect analyses

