# 2 STUDY OBJECTIVES

## 2.1 OBJECTIVES

### 2.1.1 Primary Objective

The primary objective is to determine whether it is possible to achieve acceptable recruitment and retention rates in two centres (NHS Lothian and NHS Grampian) within defined inclusion/exclusion criteria

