## 2.2 ENDPOINTS

### 2.2.1 Primary Endpoints

1. The proportion of eligible patients randomised into the study.
2. The proportion of randomised patients who take all their medication and fully complete questionnaires at final follow up.

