### 9.2 PROPOSED ANALYSES

#### (i) Determine recruitment and retention rates in two centres

Using the information collected from the participant log, we will determine the number of patients recruited from the pool of eligible women and a >50% recruitment will be deemed acceptable. While a retention rate of 100% would be ideal, we will consider a rate of 90% satisfactory. We will provide an estimate of the proportion and its 95% confidence interval. In addition, we will determine the nature and number of unanswered questions in each questionnaire and identify reasons for non-response through the focus groups and participant interviews in order to optimise data collection in the future trial.

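### Sections 9.1 and 9.2(i) use different, unreconciled criteria for acceptable retention (loss below 20% against 90% retained), and the 12/60 interval shows precision only

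*Protocol*

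**What the plan says.** The primary objective (Protocol 2.1.1) turns on what counts as acceptable: "The primary objective is to determine whether it is possible to achieve acceptable recruitment and retention rates in two centres". Three places bear on the retention half of it.

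- **Section 9.1** sizes the study "to estimate the sample size to establish feasibility based on a loss to follow-up of <20"%. It supports this with one interval: "A 95% CI for 20% of 60 patients (12/60) is 11% to 32"%. The planned number is fixed in the same paragraph: "aim to recruit 60 patients over a nine-month recruitment period".
- **Section 9.2(i)** gives the standard for the result: "While a retention rate of 100% would be ideal, we will consider a rate of 90% satisfactory". It then adds: "We will provide an estimate of the proportion and its 95% confidence interval".
- **Section 2.2.1** defines the second primary endpoint as "The proportion of randomised patients who take all their medication and fully complete questionnaires at final follow up".

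No sentence connects the 20% with the 90%, says which of the three quantities each applies to, or says whether the point estimate or a confidence limit has to meet the standard.

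**The concern.** A pilot whose primary question is whether retention is acceptable needs one meaning of acceptable, fixed in advance. Here the section that justifies the sample size and the section that describes the analysis set the bar at different levels: up to nearly 20% loss in one, at most 10% in the other. A result between the two could be reported as feasible or as falling short, depending on the section cited, and the choice could be made after the data are seen. That reading feeds directly into planning of the larger trial.

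There is a second, smaller difficulty in 9.1. The paragraph speaks of establishing feasibility at a loss below 20%, but the interval offered is the one for an observed loss of exactly 20%, and it extends to 32%.

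**Working it through.** **Inputs.** n = 60 and the 12/60 interval (9.1); loss below 20% (9.1); 90% retention satisfactory (9.2(i)); endpoint definition (2.2.1). The true loss rates used below (10%, 15%, 20%) are assumptions that span the two criteria.

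**1. Reproduce the plan's figure.** The exact (Clopper-Pearson) 95% limits for x of n are the 2.5% quantile of Beta(x, n − x + 1) and the 97.5% quantile of Beta(x + 1, n − x). For 12/60:

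| Method | 95% CI |
|---|---|
| Exact | 10.8% to 32.3% |
| Wilson | 11.8% to 31.8% |
| Jeffreys | 11.4% to 31.4% |
| Wald | 9.9% to 30.1% |

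The exact interval rounds to the stated 11% to 32%. Of these four methods it is the only one that does, so it is used below.

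**2. Put both criteria on one scale.** Assume retention = 1 − loss.

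- Loss below 20% of 60 means fewer than 12 lost, so 11 or fewer.
- Retention of at least 90% of 60 means at least 54 retained, so 6 or fewer lost.
- The criteria disagree for 7 to 11 lost: loss of 7/60 = 11.7% to 11/60 = 18.3%, retention of 88.3% to 81.7%.

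**3. How often the disagreement arises.** With X ~ Binomial(60, p), P(7 ≤ X ≤ 11) = P(X ≤ 11) − P(X ≤ 6):

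| True loss p | P(X ≤ 11) | P(X ≤ 6) | Difference |
|---|---|---|---|
| 10% | 0.985 | 0.606 | 0.38 |
| 15% | 0.819 | 0.185 | 0.63 |
| 20% | 0.449 | 0.031 | 0.42 |

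**4. What 60 women can show about 20% loss.** The exact limits for loss are:

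- 5/60: 2.8% to 18.4%
- 6/60: 3.8% to 20.5%
- 12/60: 10.8% to 32.3%

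The exact upper limit is therefore below 20% only with 5 or fewer losses. The chance of that is 44% if true loss is 10%, 10% if 15% and 1% if 20%. At 6/60 the answer depends on the method: the upper limit is 20.5% (exact), 20.2% (Wilson), 19.5% (Jeffreys) or 17.6% (Wald). Turned round, 54/60 retained has an exact interval of 100 − 20.5 = 79.5% to 100 − 3.8 = 96.2%.

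**5. The third definition.** A woman who fully completes the final questionnaires has not been lost, so the proportion meeting the 2.2.1 endpoint cannot exceed one minus loss, and it may be lower. As an illustration only: if 6 are lost and 2 more are followed up but did not take all their medication, loss is 6/60 = 10%, which meets both criteria in step 2. The 2.2.1 proportion is then 52/60 = 86.7%, which is below 90%.

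**The case against.** **The two figures may serve different purposes.** A loss of 20% could be a tolerable maximum used for planning precision, with 90% as a target. That is a coherent design, and 9.2(i) says only that 90% would be considered satisfactory, which is not a formal pass mark. The protocol never says this is the intent, though, so the possibility supports clarifying the text. It does not remove the conflict.

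**Loss and retention may not be complements.** Sections 5.5.3 and 5.5.4 separate stopping treatment from leaving the trial, and 2.2.1 requires more than being followed up. This stands: the count of 7 to 11 holds only if retention is read as one minus loss. It is also why the fix has to name the quantity as well as the threshold.

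**Stronger readings that the protocol does not support.** A reader might infer that the calculation in 9.1 is wrong. It is not, because the stated interval reproduces. A reader might infer that 60 women cannot show loss below 20%. They can, by the exact interval, if 5 or fewer are lost. An observed rate of exactly 20% could not exclude 20% at any sample size, so this is no defect of 60. Nor is the interval unrelated to the sample size: 11% to 32% is exactly what 12/60 gives. What remains is that an interval centred on the threshold shows precision there and does not establish that loss lies below it.

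**This could be left to a statistical analysis plan.** Further detail could be. Here, however, both thresholds and the sample size rationale are already stated in the protocol and do not agree.

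**Conclusion.** The point holds as an internal inconsistency of moderate severity. Sections 9.1 and 9.2(i) apply unreconciled criteria to the retention part of the primary objective, and 2.2.1 brings in a stricter definition. Under the assumption that retention is one minus loss, with 60 women and independent losses at a common rate, the two criteria give different answers for 7 to 11 losses. Across true loss rates of 10% to 20%, that happens with a probability of about 0.4 to 0.6.

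The estimate, its confidence interval and the sample size are unaffected. What is at risk is how the result is labelled and the freedom to choose the label afterwards. The wording in 9.1 claims more than its interval supports, but the interval itself is correct.

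**What to change.** 1. State one retention threshold and use it in both 9.1 and 9.2(i), applied to one named quantity aligned with 2.2.1. If two levels are intended, name one as the tolerable maximum loss and the other as the target, and say what follows from a result between them.
2. Say whether the point estimate or a confidence limit must meet the threshold.
3. Reword 9.1 as a precision statement at the chosen rate and drop the claim to establish feasibility. If 90% is kept, for example: with 60 women and 54 retained, the exact 95% confidence interval for retention is 79% to 96%; a loss of 20% is excluded by the exact interval only if 5 or fewer women are lost. If the quantity chosen is the 2.2.1 endpoint, the sentence should count women meeting that endpoint.

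Keep the sample size at 60. The cost is about one sentence in each of 9.1 and 9.2(i), with no extra participants and no change of design. The drawback is that the stated case for 60 looks less favourable: it will openly show that a result right at 90% retention does not exclude 20% loss by the exact interval.

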### 9.2 PROPOSED ANALYSES

#### (i) Determine recruitment and retention rates in two centres

Using the information collected from the participant log, we will determine the number of patients recruited from the pool of eligible women and a >50% recruitment will be deemed acceptable. While a retention rate of 100% would be ideal, we will consider a rate of 90% satisfactory. We will provide an estimate of the proportion and its 95% confidence interval. In addition, we will determine the nature and number of unanswered questions in each questionnaire and identify reasons for non-response through the focus groups and participant interviews in order to optimise data collection in the future trial.

#### (ii) Effectiveness and acceptability of proposed methods of recruitment, randomisation, drug treatments, questionnaires, use of brain fMRI and follow-up?

These areas will be explored in the focus group discussions and assessed quantitatively using additional questions included in participant questionnaires administered at 6 months. Due to the conflicting literature about the benefits of methods such as prescription monitoring, pill counting and devices for monitoring the self-administration of medicines (Melnikow and Kiefe, 1994), data on blinding and compliance to treatment will be derived from questionnaires at 6 months. We aim to determine if treatment is acceptable in terms of self-reported compliance (from treatment diaries). Although this is a pilot study and the sample size is small, we will assess the effect of any non-compliance on the LICKERT score by performing protocol and intention to treat analyses. This information along with health professionals' and clinical research nurses' views (as assessed by questionnaire) will be used to inform the design of the future RCT. (iii) Sensitivity of brain fMRI to study the effect of gabapentin in the management of CPP

The fMRI data will be analysed using a voxelwise approach and hierarchical linear modelling. An ANOVA [pre/post treatment\*gabapentin/ placebo] will be performed to investigate which areas of the brain gabapentin acts on compared to placebo. A regression analysis between brain activity and the behavioural measures will also be performed to evaluate the relationship between gabapentin brain activity and pain reduction. The brain fMRI scan results will then be compared with other studies of gabapentin (Iannetti 2005, Governo 2008) to determine the sensitivity of this approach to study the mechanism of action of gabapentin in CPP. We will use published fMRI methodology (Mumford & Nichols 2008) informed by the pilot to power future fMRI studies.

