#### **5.5.4 Withdrawal of Study Participants**

Participants may discontinue from the trial at any time at their own request, or they may be withdrawn at any time at the discretion of the Investigator or sponsor for safety, behavioural or administrative reasons. Withdrawal may be from treatment or from the whole trial. With permission all data obtained up to point of withdrawal will be used. If a participant does not return for a scheduled visit, every effort will be made to contact the participant. In any circumstance, every effort will be made to document subject outcome, if possible. The investigator will inquire about the reason for withdrawal, request that the subject return all unused investigational products, return for a final visit, if applicable, and follow-up with the subject regarding any unresolved adverse events.

If the participant withdraws from treatment then she will be unblinded and if on gabapentin she will be advised to reduce the dose according to a recognised dose reduction protocol.

If the participant discontinues from the trial and also withdraws consent for the disclosure of future information, no further evaluations will be performed and no additional data will be collected. The sponsor may retain and continue to use any data collected before such withdrawal of consent. If the participant shows signs of acute pancreatitis or falls pregnant, they will be withdrawn from treatment immediately.

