#### **6.5 PARTICIPANT COMPLIANCE**

All participants will be given a diary at randomisation and asked to document daily drug use (including self-medication and alternative treatments, eg acupuncture), side effects, reasons for drug escalation or reduction. We will also include specific healthcare resource use questions (e.g. attendance at GP, hospital). We will record the proportion of participants who completed their diaries with no missing data.

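### Acceptability and treatment-guess items are planned only at 6 months and interviewees are not sampled on withdrawal or adherence, so women who leave may be under-represented

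*Protocol*

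**What the plan says.** The first secondary objective (section 2.1.2) covers how effective and acceptable the recruitment, randomisation, drug treatment, fMRI and follow-up methods are to patients. Section 9.2(ii) gives the sources: "These areas will be explored in the focus group discussions and assessed quantitatively using additional questions included in participant questionnaires administered at 6 months". It adds that "data on blinding and compliance to treatment will be derived from questionnaires at 6 months", and then also names the treatment diaries as a source for self-reported compliance.

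Section 8 agrees on timing. The forms at 0 and 3 months carry the pain, disability, mood and quality-of-life tools. The questions on believed allocation, acceptability of the medication, compliance and data-collection methods are added only to the 6-month form.

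The qualitative arm is "A purposive sample (based on age, social class and severity of symptoms) of 10 Edinburgh women" and 10 Aberdeen women, with individual interviews offered to those who do not want a group, up to 20 in all. Section 7.2 places the groups at 3 to 6 months.

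On compliance, section 6.5 states: "All participants will be given a diary at randomisation and asked to document daily drug use". Section 7.2 lists diary collection at the 6-month visit and at no other.

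At withdrawal, section 5.5.4 provides for asking the reason, returning unused product, and asking the woman to "return for a final visit, if applicable". It also says that a woman who withdraws from treatment is unblinded. It mentions no acceptability items, treatment guess or diary return.

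**The concern.** A woman who stops because the drug, the diary or the visits were too much for her is among the least likely to complete a questionnaire at 6 months. If the acceptability items exist only there, the quantitative answer comes mainly from those who stayed. Interview sampling does not correct this, because withdrawal and adherence are not among the criteria. Leavers may be included, but nothing makes sure of it.

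Blinding has a further problem. Some women will stop treatment but remain in follow-up and return the 6-month form. By then they have been told their allocation, so what they believe they received no longer says anything about the success of the blind.

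At stake is what the pilot can tell the designers of the full trial about why women find the treatment or methods unacceptable, and whether the blind holds in those who stop early. Neither can be recovered once the contact has passed.

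**Working it through.** **1. The plan's own figure.** Section 9.1 gives a 95% CI of 11% to 32% for a loss of 12/60. The exact (Clopper-Pearson) limits are the 2.5% point of Beta(12, 49) and the 97.5% point of Beta(13, 48), which are 10.8% and 32.3%. The stated interval is reproduced.

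**2. Inputs for the size of the bias.**
- Randomised: 60 (sections 3 and 9.1).
- Lost, m: 6 (the 90% retention criterion in section 9.2(i)), 12 (the planning value in section 9.1), and 19 (the upper limit, 32% of 60 = 19.2).
- Acceptability in completers: not given. About 90% is assumed, with 80% as a check.
- Acceptability in leavers: not given. The full range from 0% to 100% is used.

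**3. Formula.** With x content completers and y content leavers, the reported figure is x/(60 − m) and the all-randomised figure is (x + y)/60. Their difference equals (m/60) × (completer rate − leaver rate).

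**4. Results, completers about 90% content.**

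| Lost | Reported | All randomised, y = 0 | All randomised, y = m | Largest overstatement |
|---|---|---|---|---|
| 6 | 49/54 = 90.7% | 49/60 = 81.7% | 55/60 = 91.7% | 9.1 points |
| 12 | 43/48 = 89.6% | 43/60 = 71.7% | 55/60 = 91.7% | 17.9 points |
| 19 | 37/41 = 90.2% | 37/60 = 61.7% | 56/60 = 93.3% | 28.6 points |

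With 12 lost and half of them content, the all-randomised figure is 49/60 = 81.7%, an overstatement of 7.9 points. If all 12 were content, the reported figure would be 2.1 points too low. With 80% assumed in completers and 12 lost, the reported figure is 38/48 = 79.2%, and the range is 38/60 = 63.3% to 50/60 = 83.3%.

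**5. The treatment guess.** This needs no assumed rate. For completers, section 7.2 lists the questionnaire ahead of unblinding at visit 4, so their guess is usable. For women who withdraw from treatment, section 5.5.4 unblinds them and no earlier guess is scheduled. No informative guess is therefore planned for them, whether or not they return the 6-month form.

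**6. Compliance.** Section 6.5 gives a daily record from randomisation. Section 7.2 schedules its collection at 6 months only, and section 5.5.4 asks a leaver for unused product but not for her diary. The record may exist up to the day she stops, but no step is laid down for retrieving it.

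**The case against.** The strongest reply is that women who leave are not lost from view, and much of it stands.

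- **Compliance.** A reader might infer that compliance is asked only at 6 months. It is not: diaries run daily, and there are weekly calls during dose escalation and a short interview at week 6. What remains is the narrower point about retrieving the diary.
- **Leavers.** Section 8 logs reasons for withdrawal and loss. Withdrawal may be from treatment alone, so some women who stop the drug can still answer at 6 months. The groups start at 3 months and nothing excludes leavers. A logged reason is still not an acceptability rating or a treatment guess.
- **Direction of the decision.** A reader might infer that the bias favours going ahead. The protocol does not support this. Primary endpoint 2 is a proportion of randomised patients, so leavers count as failures. The stated criteria are recruitment above 50% and retention of 90%, and no threshold rests on the acceptability items. A loss of 12/60 is 80% retention, which already misses the criterion.
- **Section 9.2(i).** It plans to "identify reasons for non-response through the focus groups and participant interviews", and a reader might take this as the means of explaining drop-out. It follows a clause on unanswered questions in each questionnaire, so it most naturally means skipped items.
- **Missing the leavers altogether.** A reader might also infer that the interviews would probably contain no leavers. If 20 women were drawn at random from 60 with 12 leavers, 4 would be expected, and the chance of none is C(48,20)/C(60,20) = 0.4%. The sample is purposive and the protocol does not say whether leavers stay in the frame. The point is therefore the absent criterion, not a probability.

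The denominator for reporting is commonly left to a statistical analysis plan, which is not at hand, and the flowcharts are not shown. Neither alters what the written sections schedule for collection.

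**Conclusion.** The point holds as a risk. Acceptability and treatment-guess items are specified only for the 6-month questionnaire, none are named at withdrawal, and completion status does not guide the interview sample. The secondary acceptability estimates may therefore be biased upward. With an assumed 90% or so in completers and the planning loss of 12/60, the all-randomised figure could lie anywhere from 72% to 92%. That corresponds to an error between 17.9 points too high and 2.1 points too low. The size depends on a loss rate and on leavers' views that the protocol does not supply, so it should not be read as showing that acceptability is overstated.

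The blinding part is firmer, since it follows from the text alone: women who withdraw from treatment are unblinded with no guess scheduled beforehand. The primary endpoints are not affected. This is a cheap improvement on a secondary objective, and it has to be made before the withdrawal contacts take place.

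**What to change.** 1. **Section 5.5.4.** At the withdrawal contact, by visit or phone and where the woman agrees, ask the same short acceptability, compliance and treatment-guess items as in the 6-month questionnaire. Ask them before the code is opened in routine cases. Emergency unblinding under section 5.5.3 is left untouched. Request the diary at the same contact, alongside the unused product.
2. **Section 8, focus groups.** Add completion status (withdrew, poor adherence, incomplete forms) to the purposive criteria, within the same 20 places, and state that women who have left remain eligible for invitation.
3. **Section 9.2(ii).** Report acceptability out of all randomised women, with lower and upper bounds that count those still missing as all negative and all positive. Show the treatment guess separately for women asked at withdrawal and at 6 months.

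The cost is one short form at a contact that the protocol already foresees, and a changed sampling list. The limits should be acknowledged: the final visit is conditional, some leavers will decline, and those who withdraw consent for further data cannot be asked. The bounds would narrow but not close.
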